### Randomization, allocation concealment, and blinding

Before randomization, a researcher not involved in subject recruitment and data collection will prepare a randomization list with 100 sets of numbers, using Research Randomizer software.^1^ The study subjects will be randomly divided into an intervention group and a control group in a 1:1 ratio by personnel who will not directly participate in this study. Then, random numbers will be assigned to the selected groups of research subjects, and they will be sorted from small to large according to the size of the random numbers. The first half will be the control group, and the second half the intervention group. The random numbers will be sealed and handed over to personnel responsible for random allocation for proper safekeeping. They will not participate in the inclusion of the study subjects and subsequent intervention processes. However, because of the nature of this intervention, it would not be not possible to blind the participants and intervention staff, although the data collectors and statisticians in the study will be blinded.

### Sample

The recruitment and screening of all participants were conducted on the online platform of Fujian Provincial Hospital’s WeChat official account or the hospital’s offline wound treatment clinic. This is a randomized controlled trial consisting of two branches and three evaluation stages (T0, baseline; T1, 12-week post intervention; T2, 24-week follow-up). The intervention-group participants received DE-HBWC project wound treatment at their own homes, while the control group participants received treatment at traditional hospital wound-treatment clinics. The required sample size was estimated using PASS v15.0 (NCSS, LLC, United States), based on a completely random design, to compare the mean values of two independent samples. Based on our previous wound treatment results for the healing time of chronic wounds and using two-sample T-tests assuming equal variance procedure of PASS v15.0, μ1 = 38.64, μ2 = 32.54, *σ* take 8.21, a sample size of 40 participants per group was determined to be sufficient to detect an effect with a type 1 error rate of 5 and 90% power. Assuming a drop-out rate of 20%, a total of 100 participants will be needed, with 50 participants in each group.

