Nurse home visits are scheduled biweekly, informed by evidence-based guidelines and optimized for resource efficiency. Frequency adjustments follow predefined clinical criteria (e.g., wound progression, infection signs) and are approved by the supervising physician. Remote monitoring data (e.g., wound images) inform visit prioritization, ensuring high-risk patients receive timely in-person care. Wound specialist nurses completed a four-stage competency-based training program, including theoretical instruction, technical skill simulations, protocol-specific workflows, and ongoing supervision. The Nursing Department monitors fidelity by reviewing protocol deviations on a weekly basis. The dressing change is customized by the wound specialist nurse to the individual patient’s situation in regard to the wound. The duration of the intervention was 12 weeks; if the patient’s wound was completely healed before 12 weeks, there was no dressing change—only assessment and guidance; however, if the wound was not healed after 12 weeks, the intervention could be continued according to the patient’s wishes. Patients with chronic wounds are consulted through the developed internet hospital, and data such as basic patient information, questionnaires, and wound pictures are managed using the chronic disease management system already developed by the hospital.

We aim to create a supportive system for patients with chronic wounds. This includes an online community where patients can share their care experiences and feel less isolated. We also provide easy-to-understand educational materials like animated videos and illustrated medication guides, which are sent out weekly through our chronic disease management platform. Additionally, we offer a 24-h nursing hotline. Trained wound nurses will be available to answer urgent questions from families, such as what to do if a wound starts bleeding or gets worse. To ensure participants follow the program guidelines, we use a game-based incentive system. Participants can earn points by uploading wound photos, reading health education materials, completing assessments, or joining activities. These points can be exchanged for nursing supplies or used to book services more quickly. Wound care reminders are customized based on each patient’s daily routine. We also send personalized reminders for wound care based on each patient’s routine.

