### Data collection and statistical analysis

Enrolled subjects will be scheduled to complete the baseline data collection. Data will also be collected after 12 and 24 weeks for outcomes, and data on the primary outcome, wound healing, will be collected biweekly. All data analysis will be performed using SPSS Statistics v21.0 (IBM). A two-tailed approach will be used, with *α* level set to 0.05 for testing. To ensure that outcome evaluators and data analysts are not influenced by group assignment, they will not interact with participants, except in the case of outcome evaluators during data collection. Descriptive statistics will be used to summarize demographic and other baseline characteristics. Tests of normality of data distribution were validated using Kolmogorov–Smirnov. After approaching normality for each variable, two-sample independent *t*-tests, x^2^-tests (or Fisher’s exact tests), or nonparametric tests, as appropriate, were used to compare normally distributed variables between the intervention and control groups. If necessary, the results will be adjusted based on potential confounding factors such as age, gender, and education level. Statistical analysis will be based on the intention-to-treat (ITT) method (34).

Generalized linear mixed effects models (GLMM) will be used to estimate the odds ratio (OR) and 95% confidence intervals (CIs) for assessing whether changes in outcome indicators are significantly different over time. Models include randomized groups with time as a fixed effect and time × group as an interaction effect to account for the correlation between repeated observations for each participant. Characteristics such as patient age, gender, wound type, and wound size will be adjusted for as covariates. In addition, to explore the effect of baseline characteristics on intervention effect sizes, we will conduct subgroup analyses by testing for interactions between subgroups and intervention effects. Predefined subgroup analyses will be conducted for baseline characteristics including age, gender, education, monthly income, wound type, and wound size. The main outcomes of the subgroup analyses are *p*-values for the group × time × characteristics interaction coefficients and estimates (95% CIs) of the differences between the intervention and control groups within each subgroup. Finally, sensitivity analyses will be performed by interpolating missing data using a random forest model to improve the reliability of our findings.

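### Healing time, the only powered endpoint, is planned as a difference in means, and no listed analysis handles wounds not seen to heal

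*Protocol article*

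**What the plan says.** **Sample.** The calculation is set up "to compare the mean values of two independent samples", from earlier results "for the healing time of chronic wounds and using two-sample T-tests assuming equal variance procedure of PASS v15.0". The inputs are "μ1 = 38.64, μ2 = 32.54", with no unit, and for the SD "take 8.21, a sample size of 40 participants per group was determined to be sufficient", at a "type 1 error rate of 5 and 90% power". A 20% drop-out allowance raises 40 per group to 50. No other endpoint has a power calculation.

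**Study outcome measures.** Healing duration is one item of the wound treatment table, which is listed with the BWAT under the primary outcomes. Table 2 schedules the BWAT and wound treatment table every two weeks and 3D images weekly during the intervention, then assessments at weeks 12 and 24 with none between.

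**Intervention, DE-HBWC arm.** The intervention lasts 12 weeks, but "if the wound was not healed after 12 weeks, the intervention could be continued according to" the patient's preference.

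**Data collection and statistical analysis.** "A two-tailed approach will be used". The tests named are t-tests, chi-square or Fisher tests "or nonparametric tests, as appropriate, were used to compare normally distributed variables between the intervention and control groups", plus a generalized linear mixed model giving odds ratios. The analysis is by intention to treat. Random-forest imputation appears as a sensitivity analysis.

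**Criteria for discontinuing or modifying allocated interventions.** Assessments not completed after withdrawal count as missing.

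**The concern.** A wound that has not healed when observation ends has no healing time. What is known is that the time exceeds the last assessment, which is censoring. A comparison of means needs a value for every patient, so such patients must be left out or assigned a number.

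Leaving them out selects patients on something that happens after randomisation and may differ by arm. That is not an intention-to-treat comparison, and the stated 90% power does not carry over to it. Ordinary imputation of a missing value does not by itself use the fact that the wound was still open at a known date.

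At stake is the one endpoint that justifies the sample size.

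**Working it through.** **1. The plan's own figure.** Difference 38.64 − 32.54 = 6.10; standardised effect 6.10/8.21 = 0.743. By the exact noncentral t, two-sided 5% and 90% power need 39.05, rounded up to 40 per group (power 90.7% at 40, 89.96% at 39). A one-sided test would need 32 and does not match. 40/(1 − 0.20) = 50 per group, 100 in total. The figure reproduces.

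**2. Do the planning figures leave room for censoring?** The unit must be assumed. Weeks would leave 96% of control and 85% of intervention wounds unhealed at week 24, so days is the sensible reading. Week 12 is day 84:

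- Control: (84 − 38.64)/8.21 = 5.5 SD above the mean, P(unhealed) about 2 × 10⁻⁸.
- Intervention: (84 − 32.54)/8.21 = 6.3 SD, about 2 × 10⁻¹⁰.

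In simulated trials with these figures, 50 per arm and 20% dropping out at random times, the mean difference among patients seen to heal is 6.08 against the true 6.10. The t-test has 93.7% power and log-rank 90.1%. In this case nothing material goes wrong.

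**3. If wounds stay unhealed (assumed).** The documents give no healing proportion. Assume exponential healing, 50 per arm, no drop-out, cut-off day 84, hazard ratio (HR) intervention to control.

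Restricted mean to day 84 = (1 − e^(−84λ))/λ. With 70% of controls healed, λ = −ln(0.30)/84 = 0.01433, giving 0.70/0.01433 = 48.8 days. With HR 1.8, λ = 0.0258, giving 34.3 days. The difference is 14.5 days.

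Results over 60–80% of controls healed by day 84:

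| HR | t-test, healed wounds only | t-test, unhealed set to 84 | Log-rank |
|---|---|---|---|
| 1.8 | 12–34% | 62–76% | 69–78% |
| 1.5 | 9–16% | 34–43% | 38–47% |

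For HR 1.8 the healed-only difference is 4.8–7.2 days, while the restricted mean difference is about 14.

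**4. Direction (assumed mixtures).** A fixed share never heals by day 84; the rest heal with SD 8.21.

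- 30% of control and 10% of intervention wounds unhealed, all healers at mean 38.64. Restricted means: 0.7 × 38.64 + 0.3 × 84 = 52.2 and 0.9 × 38.64 + 0.1 × 84 = 43.2, a benefit of 9.1 days. The healed-only difference is about 0; the t-test rejects in about 5% of trials, log-rank in 62%.
- 10% of control and 30% of intervention wounds unhealed, healers at 38.64 and 32.54. Restricted means: 0.9 × 38.64 + 0.1 × 84 = 43.2 and 0.7 × 32.54 + 0.3 × 84 = 48.0, a disadvantage of 4.8 days. The healed-only t-test still favours the intervention in about 91% of trials.

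**5. What a time-to-event analysis would need.** Healing events for 90% power = 4(1.960 + 1.282)²/(ln HR)²: 256 for HR 1.5, 135 for 1.75, 88 for 2.0. With 80 events, power is 44%, 71% and 87%. No single corrected sample size follows, because the plan states no hazard ratio.

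**The case against.** **The plan does not say that unhealed wounds are dropped.** This stands. The list of tests is generic; the link from t-test to healing time comes from the Sample section. A reader might infer a healed-only analysis, but no sentence prescribes one, and an SAP not shown may say more. Still, none of the methods named is built for censored times.

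**Setting unhealed wounds to 84 days nearly solves it.** Largely true without drop-out: it trails log-rank by a few points and estimates the 12-week restricted mean difference. A rank test with unhealed wounds ranked last is also defined. Neither deals with a patient lost before healing, and the plan states neither rule.

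**Healing information does not rest on one time point.** This stands. A reader might infer that a healed/unhealed comparison would be 100% vs 100% and so useless. That is true only at weeks 12 and 24. Assessments are biweekly, and the planning figures imply about 10% vs 29% healed at day 28 and 66% vs 88% at day 42, which a repeated-measures model can use. The BWAT is also a primary measure.

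**Unhealed wounds are a contingency, and week 24 is still to come.** Partly. The 12-week sentence is conditional, the exclusion criteria remove some non-healing wounds, and patients who leave after healing keep their time. But healing after week 12 may be dated only to within 12 weeks. By then treatment continues by choice, and the Scale section has the intervention group entering a further randomised incentive trial.

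**Log-rank is not always better.** True. If 30% stay unhealed in both arms and only healers' speed differs, the healed-only t-test has about 85% power and log-rank 18%. The t-test is then answering a narrower question, confined to patients who heal.

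**Conclusion.** The point holds in conditional form. Healing time carries the whole sample size, is planned as a mean, and has no listed method for censored times, while the protocol itself allows for unhealed wounds and drop-out.

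A reader might infer that the treatment effect will be distorted. The documents do not support that: under the planning mean and SD, read as days, censoring at week 12 is practically nil and random drop-out moves the difference only from 6.10 to 6.08.

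The harm depends on two things the document does not state: how many wounds stay unhealed, and how patients without a healing date are handled. With 20–40% of control wounds unhealed and a healed-only comparison, power falls to about 12–34% (HR 1.8) where log-rank keeps 69–78%, and unequal unhealed shares can hide or reverse the result. These sizes rest on assumed exponential or mixture healing. The exponential has SD equal to its mean, far from the 8.21 in the plan, so they illustrate the risk and do not predict this trial.

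**What to change.** State in the protocol and SAP:

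1. Healing time is the time from randomisation to complete healing. Wounds unhealed at 12 weeks are censored there, since no assessment is scheduled between weeks 12 and 24. Drop-outs before healing are censored at their last wound assessment.
2. The test is log-rank, with a Cox hazard ratio adjusted for wound type and baseline wound size (both already named as covariates).
3. The 12-week restricted mean difference in days is reported alongside, which keeps the planning scale.
4. The unit of the planning means is given. The 90% power is stated to hold only for fully observed, normally distributed healing times, and power is restated for the time-to-event analysis under stated healing proportions and hazard ratios.

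The cost is wording and one power calculation; the weekly and biweekly wound data are already planned. Under the planning figures log-rank with 50 per arm and 20% drop-out still has about 90% power. The downside is that the restated power may look less favourable if many wounds are censored. Censoring drop-outs at their last assessment assumes that leaving is unrelated to healing prospects, which should be said.

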#### Intervention, DE-HBWC arm

The DE-HBWC program was devised through three phases of crafting the research questions, EBP, identifying the barriers and facilitators to intervention implementation, and, ultimately, through meetings with experts and pre-experiments. The DE-HBWC program is a personalized one-on-one treatment program for chronic wound patients delivered by specialist wound nurses using a combination of online and offline intervention modes. Conducting remote video visits through electronic facilities weekly to evaluate wounds and provide guidance on dressing changes online, and offline home medication change, assessment, and health guidance services are provided by wound specialist nurses every 2 weeks. During weekly remote assessments, all aspects of wound care are carefully assessed by a wound specialist nurse and documented with the assistance of a graduate nursing student. This includes wound morphology, which encompasses tissue type, dimensions, and color profiles, as well as exudate metrics such as volume, consistency, and the presence and severity of odor. The assessment also evaluates the periwound status, focusing on skin integrity, sinus tract characteristics, and signs of infection. Furthermore, pharmacological interventions are thoroughly recorded, including antimicrobial therapies and adjunctive agents, along with detailed application protocols. Lastly, the documentation tool supports intervention tracking by capturing dressing protocols, debridement frequency, and the provision of health education to patients and caregivers.

Nurse home visits are scheduled biweekly, informed by evidence-based guidelines and optimized for resource efficiency. Frequency adjustments follow predefined clinical criteria (e.g., wound progression, infection signs) and are approved by the supervising physician. Remote monitoring data (e.g., wound images) inform visit prioritization, ensuring high-risk patients receive timely in-person care. Wound specialist nurses completed a four-stage competency-based training program, including theoretical instruction, technical skill simulations, protocol-specific workflows, and ongoing supervision. The Nursing Department monitors fidelity by reviewing protocol deviations on a weekly basis. The dressing change is customized by the wound specialist nurse to the individual patient’s situation in regard to the wound. The duration of the intervention was 12 weeks; if the patient’s wound was completely healed before 12 weeks, there was no dressing change—only assessment and guidance; however, if the wound was not healed after 12 weeks, the intervention could be continued according to the patient’s wishes. Patients with chronic wounds are consulted through the developed internet hospital, and data such as basic patient information, questionnaires, and wound pictures are managed using the chronic disease management system already developed by the hospital.

We aim to create a supportive system for patients with chronic wounds. This includes an online community where patients can share their care experiences and feel less isolated. We also provide easy-to-understand educational materials like animated videos and illustrated medication guides, which are sent out weekly through our chronic disease management platform. Additionally, we offer a 24-h nursing hotline. Trained wound nurses will be available to answer urgent questions from families, such as what to do if a wound starts bleeding or gets worse. To ensure participants follow the program guidelines, we use a game-based incentive system. Participants can earn points by uploading wound photos, reading health education materials, completing assessments, or joining activities. These points can be exchanged for nursing supplies or used to book services more quickly. Wound care reminders are customized based on each patient’s daily routine. We also send personalized reminders for wound care based on each patient’s routine.

The program is overseen by a wound care specialist physician who is responsible for reviewing patient progress biweekly through electronic records. This physician also approves any necessary adjustments to treatment plans. Nursing graduate students are responsible for assisting with text recording and data organization. Additionally, nurses play a pivotal role in coordinating care with primary care providers utilizing the hospital’s integrated electronic health record system, ensuring seamless communication and continuity of care. The Deputy Director of Nursing is responsible for overseeing the project implementation and ensuring quality control. Patients are provided with access to a telehealth hotline designed to address urgent concerns, such as sudden onset of pain, fever, or purulent drainage. This resource ensures that patients can promptly seek assistance for complications that may arise during their treatment. The escalation protocol ensures tiered clinical responses: (1) patients with suspected wound deterioration (e.g., increased erythema, purulent drainage, or systemic symptoms) initiate real-time telehealth consultations with certified wound specialist nurses; (2) nurses triage cases to physicians for urgent directives, prioritizing same-day in-person evaluations for high-risk scenarios; and (3) physicians determine hospitalization needs based on standardized severity criteria (e.g., sepsis risk, necrotizing infection).

#### Control, TH arm

Participants in the control group underwent offline traditional treatment at the Wound Treatment Clinic of Fujian Provincial Hospital, and the intervention cycle and dressing change principles were the same as those for the intervention group. Patients in the control group attended the Wound Treatment Clinic every other day for dressing change, assessment, and health guidance. The frequency of dressing changes is flexibly adjusted by the wound specialist nurses according to the patient’s patient wound healing status. Wound specialist nurses delivered the interventions, while nursing graduate students collected patient data using the hospital’ s in-house chronic disease management platform.

### Study outcome measures

The primary outcome measures are wound healing based on the commonly used Bates-Jensen Wound Assessment Tool (BWAT) (28) and the Wound treatment table, which was formulated by our team, based on previous research (29), to evaluate the size, depth, and exudation of chronic wounds; drugs; dressings used for treatment; cost; healing duration; as well as the round-trip transportation and waiting time. Wound images will be acquired weekly and recorded and analyzed using Three Dimensions (3D) AI reconstruction technology. Empirical evidence demonstrates that 3D wound measurement devices achieve comparable accuracy to traditional nurse-performed measurements using manual scales (*p* > 0.05), while significantly reducing procedural time (*p* < 0.05) (30). Caregivers or patients can upload wound photographs through a smartphone application. The AI system automatically generates a 3D model of the wound and identifies areas that require attention, such as those with a “high infection risk.” This tool is particularly beneficial for rural or homebound patients, as it enables specialists to conduct remote assessments of wounds, thereby minimizing the necessity for in-person visits. The secondary outcome measures included participants’ quality of life, health status, wound self-management, satisfaction, and cost-effectiveness. The Chronic Wound Patient Quality of Life Scale (Wound-QoL) (31), Chronic Wound Self-Management Scale (32), and the 36-Item Short Form Survey (SF-36) (33) will be used to evaluate health, quality of life, and wound self-management. Satisfaction survey forms will be used to measure patient satisfaction with wound care. The economic benefits of intervention measures will be evaluated by measuring the cost–benefit and incremental cost–benefit ratio of wound care for the two groups of participants. More information about the sensitivity and specificity of the assessment methods can be found from the reference 28, 29.

All outcome measures and assessment time points are shown in Table 2.

**Table 2 tab2:** Assessment outline and timelines.

Measures/time point	Pre-intervention	Intervention period	Post-intervention	Follow-up
	0 weeks		12-week	24-week
Eligibility assessment				
Inclusion criteria	×			
Exclusion criteria	×			
Informed consent	×			
Allocation	×			
Intervention				
DE-HBWC group				
Traditional hospital treatment control group				
Demographics and other baseline characteristics	×			
Primary outcomes				
Wound healing (BWAT, Wound treatment table)	×	× (Biweekly)	×	×
Wound healing(3D AI wound image)	×	× (weekly)	×	×
Secondary outcomes				
Quality of life (Wound-QoL)	×		×	×
Self-management ability (WSMS)	×		×	×
Health status (SF-36)	×		×	×
Economic effect (CER, ICER)			×	
Satisfaction (Satisfaction survey form)			×	

×, Time point in the trial at which the assessment took place. ◆, Start or end time point of the trial. BWAT, Bates-Jensen Wound Assessment Tool. 3D, Three Dimensions. AI, artificial intelligence. Wound-QoL, Chronic Wound Patient Quality of Life Scale. WSMS, Chronic Wound Self-Management Scale. SF-36, 36-Item Short Form Survey. CER, cost-effectiveness ratio. ICER, incremental cost-effectiveness ratio.

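### No single healing variable is named as the deciding primary outcome, so the stated 5% error and 90% power do not attach to a defined primary test

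*Protocol article*

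**What the plan says.** Under Study outcome measures, the protocol article opens with "The primary outcome measures are wound healing based on the commonly used Bates-Jensen Wound Assessment Tool (BWAT") and adds a wound treatment table devised by the team. That table records wound dimensions and exudate, the drugs and dressings applied, and also "cost; healing duration; as well as the round-trip transportation and waiting time".

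Table 2 has two rows under primary outcomes. One is "Wound healing (BWAT, Wound treatment table"), collected at baseline, biweekly, and at 12 and 24 weeks. The other is "Wound healing(3D AI wound image"), collected at baseline, weekly, and at 12 and 24 weeks.

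Data collection and statistical analysis uses the singular: "data on the primary outcome, wound healing, will be collected biweekly". The only significance level is general: "A two-tailed approach will be used, with *α* level set to 0.05 for testing".

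The Sample section bases its calculation on healing time from the team's previous results, compared by a two-sample t-test, and concludes that "a sample size of 40 participants per group was determined to be sufficient to detect an effect". It does not say that healing time is the primary outcome.

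**The concern.** A confirmatory trial needs one declared test, or a declared rule for several, to which its error rate and power apply. Here the three places that should agree do not settle on one variable:

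- the outcome section and Table 2 offer several measures over several time points;
- the analysis section gives only a concept, wound healing;
- the sample size uses one item, healing duration, which sits inside the table.

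As written, BWAT, wound size, the 3D image or healing duration could each be presented as the primary result once the data are in. The wound treatment table also holds items that are not healing at all: drugs, dressings, cost, travel and waiting time. If those were read as primary results, a difference in them could be reported under the primary heading without any effect on wounds.

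**Working it through.** **1. The plan's own figure.** Inputs from the Sample section: means 38.64 and 32.54 (unit not stated), SD 8.21, type 1 error 5%, power 90%, drop-out 20%.

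- Difference = 38.64 − 32.54 = 6.10; standardised difference = 6.10 / 8.21 = 0.743.
- Non-centrality with 40 per group = 6.10 / (8.21 × √(2/40)) = 3.32, on 78 degrees of freedom.
- Two-sided 0.05 t-test power: 0.8996 with 39 per group, 0.907 with 40. So 40 is the smallest size reaching 90%.
- Drop-out: 40 / (1 − 0.20) = 50 per group, 100 in total.

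The arithmetic is right for one comparison of mean healing time. The fault lies in the endpoint definition, not in the calculation.

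**2. What is listed as primary.** There are three instruments: BWAT, the wound treatment table and the 3D AI image. Opening up the table gives size, depth, exudation, drugs, dressings, cost, healing duration, transportation time and waiting time, which is nine items. With BWAT and the image the total is 11, or 10 if travel and waiting count as one. Leaving travel and waiting out, because the setting of care determines them, gives 11 − 2 = 9.

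**3. Conditional false-positive chance.** Assume that each of k measures is tested once at two-sided 0.05, that none truly differs, and that any one significant result is claimed as success. Under independence the chance is 1 − 0.95^k:

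- k = 3: 1 − 0.95³ = 0.143
- k = 9: 1 − 0.95⁹ = 0.370

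The article gives no correlations, so a common correlation between the test statistics is assumed:

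| Assumed correlation | k = 3 | k = 9 |
|---|---|---|
| 0 | 14.3% | 37.0% |
| 0.3 | 13.6% | 32.6% |
| 0.5 | 12.5% | 26.9% |
| 0.7 | 10.9% | 20.2% |
| 0.8 | 9.8% | 16.5% |
| 0.9 | 8.4% | 12.4% |

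Repeated visits are not counted, because the plan models them jointly in a mixed model and does not state a test at each visit.

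**4. Power if several were kept.** With three co-primary instruments and a Bonferroni level of 0.05/3 = 0.0167, power for healing time with 40 per group falls from 0.907 to 0.807. Restoring 90% takes 51 per group, or 51 / 0.80 = 63.75, rounded up to 64, after drop-out. That is 128 in total instead of 100.

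**5. Travel and waiting.** The Control, TH arm section has controls attending the clinic every other day. The Sample section has the intervention arm treated at home. A difference in clinic travel and waiting follows from those two arrangements and carries no information about healing.

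**The case against.** The strongest defence is that the article does mean one outcome. The analysis section uses the singular, and both primary rows of Table 2 are labelled wound healing. On that reading the wound treatment table is a record form, and drugs, dressings, cost, travel and waiting time are fields on it, not endpoints. Further, the 0.05 level is general and no test is listed per item. No rule says that one success suffices. Ordering and multiplicity adjustment could properly sit in an analysis plan that is not shown. The article also reports that 3D and manual measurement have comparable accuracy, so size measures may correlate strongly, which favours the lower ends of the ranges. Cost is not simply duplicated either: the secondary outcome is cost-effectiveness, which needs recorded cost as its input.

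Much of this stands. A reader might infer that about ten measures will all be tested at 0.05, or that a significant primary result is almost certain because of travel and waiting time. The documents support neither. Both need every field of the table to count as a primary result, while the analysis section and Table 2 call the outcome wound healing.

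What the defence does not answer is which healing measure decides. Even if the table is only a form, BWAT, healing duration and the 3D image still compete, at several time points. The identity of the primary outcome is something this article does fix, so this is more than detail left to another document.

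**Conclusion.** The point holds in this form: the plan lists several primary healing measures, powers one of them, and designates none. The 5% error and 90% power are correct for a t-test on mean healing time but are not tied to a declared primary test.

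The size is conditional. It is about 8–14% for any one of three instruments and about 12–37% for nine items, over assumed correlations from 0.9 down to 0 and under an any-one-wins rule that the article does not state. These figures show what the wording leaves open; they do not estimate what the investigators will do.

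Travel and waiting time are a problem only if read as primary results. In that case the comparison reflects where care is given and says nothing about healing.

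A reader might also infer that the sample size was built on time to complete healing. It was not: the Sample section compares mean healing times and mentions no censoring.

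**What to change.** Designate one primary healing variable with its time frame, tested once at two-sided 0.05, and use the same wording in Study outcome measures, Table 2, Sample and the analysis section. Healing duration is the natural candidate because it is what was sized: analysed as a comparison of means, it leaves 40 evaluable and 50 randomised per group, 100 in total. The intervention section allows for wounds still unhealed at 12 weeks. If the sponsor therefore prefers a time-to-event analysis with those wounds censored, the power must be recalculated and restated, since the present calculation does not cover it.

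Make BWAT, wound size, depth, exudation and the 3D image secondary. Keep drugs and dressings as treatment records. Report cost, travel and waiting time in the economic evaluation.

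The cost is a change of protocol wording and a registry update, with no added patients if healing duration is analysed as sized. The price for the sponsor is that the other healing measures can no longer carry the primary claim.
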